## Abstract

**Background**: About 10% of all newborns may have difficulty breathing and require support by trained personnel. In Peru, 90% of deliveries occur in health facilities. However, there is not a national neonatal resuscitation and certification program for the public health sector. In addition, the Andes and the Amazon regions concentrate large rural remote areas, which further limit the implementation of training programs and the accomplishment of continuous certification. Neonatal resuscitation training through the use of information, communication and technology (ICT) tools running on computers, tablets or mobile phones, may overcome such limitations. This strategy allows online and offline access to educational resources, paving the way to more frequent and efficient training and certification processes.

**Objective**: To evaluate the effects of a neonatal resuscitation training and certification program that uses a multi-platform ICT (MP-ICT) strategy on neonatal health care in remote areas.

**Methods**: We propose to conduct the study through a cluster-randomized trial, where the study and analysis unit is the health care facility. Eligible facilities will include primary and secondary health care level facilities that are located in provinces with neonatal mortality rates higher than 15 per 1,000 live births. We will compare the proportion of newborns with a heart rate ≥100 beats per minute at two minutes after birth in health care facilities that receive MP-ICT training and certification implementation, with those that receive standard training and certification.

**Discussion**: We expect that the intervention will be shown as more effective than the current standard of care. We are prepared to include it within a national neonatal resuscitation training and certification program to be implemented at national scale together with policymakers and other key stakeholders.

**Trial registration**: ClinicalTrials.gov Nº NCT03210194

**Status of the study**: This study is enrolling participants by invitation only.

Study protocol version 1.1 – March 31st, 2017

## Introduction

### Background

Approximately 10% of newborns may have difficulty breathing at birth and require urgent support from trained personnel
^1^. The first 60 seconds of life in those conditions require immediate and effective interventions to help infants survive
^2^. Unfortunately, some newborns in low- and middle-income countries do not have access to appropriately trained personnel, making asphyxia one of the leading causes of neonatal death in those settings
^3^.

In Peru, about 550,000 births occur per year (Peruvian Institute for Statistics and Informatics 2015;
https://www.inei.gob.pe), and this means that approximately 6 newborns each hour may require respiratory support at birth. Problems in training health workers for adequate support of newborns is aggravated by a high turnover rate of personnel, particularly in small cities and rural areas, which hampers regular conduction of local training programs, even if they are perceived as a positive incentive
^4^. Peru is a high-middle-income country that has made significant progress in reducing neonatal and infant mortality in the last decade, despite inequities in access to health services, especially in rural areas of the Amazon and the Andes
^5,
6^. In the years 2011–2012, the Peruvian neonatal mortality rate was estimated at 12.8 per thousand live births
^7^, with an estimated 20 per thousand live births for Pasco and Cusco regions, 15 for Ayacucho and Amazonas, 12 for Huancavelica and 8 for Lima
^8^. From 2000 to 2013, neonatal mortality in Peru fell by 51% from 16.2 deaths per 1000 livebirths to 8.0
^9^.

The Neonatal Resuscitation Program (NRP) from the American Academy of Pediatrics, includes evidence-based clinical guidelines and was designed to train health care providers and instructors in hospital settings. The NRP is a paid course that has 2 components, an online component (internet-dependent) and a practice/evaluation component
^1,
10^. A variant of the NRP program is the Helping Babies Breath (HBB) program, which was designed to provide neonatal resuscitation training in resource-poor settings. The HBB has shown to reduce neonatal mortality and it is proposed as a successful global intervention
^11^. However, the greatest limitation of these programs is the need for recurrent training with a frequency of less than 12 months to maintain the acquired skills and knowledge
^12^.

One of the few neonatal resuscitation programs that has been successfully implemented outside the United States is the Neonatal Resuscitation Program from the Brazilian Society of Pediatrics, which was implemented in 1991 (Brazilian Society of Pediatrics. Neonatal Resuscitation Program (Brazilian NRP);
http://www.sbp.com.br/reanimacao). In Peru, despite several attempts made by the Social Security (Essalud) and the Ministry of Health
^13–
16^, there is still no national neonatal resuscitation program in place.

A training system using multi-platform information, communication and technology (MP-ICT) offers reliable and easier access to information and training packages from different locations, which can be implemented even in rural settings without access to the internet
^17^. Platforms may be available online, and users can download the training content through a PC, tablet or mobile phone
^18^. The training content may be repeatedly available after download, even in remote areas without access to internet.

Our study aims to evaluate the performance of a continuous process of training and certification in neonatal resuscitation in primary and secondary health facilities in the departments of Ayacucho and Cusco, through the use of MP-ICT. It aims at providing proof of concept of the intervention, which then could be incorporated as a component of a national neonatal resuscitation program to be implemented nationwide.

### Choice of comparator

The traditional way to train and certify health care professionals is through administration of a conventional theoretical course, reinforced subsequently by a practical component. This modality requires face-to-face contact between trainers and trainees. Health workers need to move from their job site to the instruction sites, usually located in the capital city of the department or in the capital city of the country. This poses economic and logistic challenges to both health authorities and health workers, and results in erratic frequency and low uptake of training courses.

Since most of the deliveries in our study region are attended by nurses and midwives, and there is a scarcity of local based doctors, we are going to use hospital based instructors as NRP trainers. This traditional training was considered as standard control, and it has been selected as the comparator for our MP-ICT intervention, because a comparison using placebo or no-training was considered to be unethical.

### Research hypothesis

The use of MP-ICT for training and certification in neonatal resuscitation will increase the proportion of children with heart rate equal or greater than 100 beats per minute at two minutes of life, as compared to standard training.

### Primary objective

To evaluate the effects of the use of a MP-ICT for training and certification on neonatal resuscitation in first and second level health facilities of Ayacucho and Cusco departments.

### Secondary objectives

To assess intervention and control efficacy in selected health facilities, in order to compare: 1) Time to start positive pressure ventilation after birth; 2) Time to achieve heart rate greater or equal than 100 per minute; 3) Apgar at 1 minute and at 5 minutes; 4) Use of supplemental oxygen after 10 minutes of life; 5) Inspiratory oxygen fraction needed at 30 minutes after birth; 6) Mortality rate during the first 7 days of life; 7) Number of referrals to health facilities with greater resolution capacity during the first 7 days of life; 8) Number of certified health professionals as providers.; and 9) Number of certified health professionals as instructors.

The efficacy of the evaluation will be evaluated at 6 months after the intervention.

Status of the study: This study is ongoing.

Study protocol version 1.0 – March 31th, 2017.

Trial registration data can be found in
Supplementary File 1.

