## Research methodology and experimental plan

### Settings

Ayacucho and Cusco are two Peruvian regions located to the south of the country. Both regions were selected as thay have a neonatal mortality rate above 15 per 1,000 live births and they are accessible through air travel. These regions cover areas of Andean highlands, but their territory is mainly on the Amazon rainforest (Peru Export and Tourism Promotion Board, 2017;
http://www.peru.travel). Also, in those departments there is the “Valley of the Apurímac, Ene and Mantaro Rivers”, also known as the VRAEM, which is extremely poor and one of the major areas of coca growing in Peru
^19^.

According to the Peruvian Registry of Institutions that Provide Health Services (RENIPRESS), Ayacucho has 418 and Cusco 848 registered health facilities (
*Registro Nacional de Instituciones Prestadoras de Servicios de Salud 2017* website;
http://www.minsa.gob.pe/portalweb/02estadistica/estadistica_2.asp?sub5=2). However, last year (2016) almost 15,000 deliveries were attended at 80 public health facilities of primary and secondary level, which represents 50% of all deliveries in both regions (
*Sistema de Registro del Certificado de Nacido Vivo en Linea* 2017 website;
http://www.minsa.gob.pe/cnv/).

Basic teams are composed by doctors, nurses, midwives and nurse technicians, who are registered in a database updated by the health personnel observatory reports (
*Observatorio de recursos humanos en salud* 2017 website;
http://observatorio.inforhus.gob.pe/). This observatory states that, up until June 11
^th^, 2017, Ayacucho had 337 doctors, 726 nurses, 466 midwives and 743 nurse technicians; while Cusco had 661 doctors, 942 nurses, 486 midwives and 806 nurse technicians.

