### Inclusion and exclusion criteria

Primary and secondary level facilities located in Ayacucho and Cusco that have a neonatal mortality rate higher than 15 per 1,000 livebirths will be eligible. Health facilities whose authorities refuse participation of their health professionals, facilities with less than 290 births a year, facilities located at more than 210 kilometers from the department capital, and those located in high-risk areas due to social unrest will be excluded. Health professionals who attend deliveries and accept their voluntary participation will be included after signing informed consent forms.

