### Randomization

Computer-generated random numbers will be used to assign the selected health facilities to either MP-ICT training (Intervention Group) or to standard training (Control Group). There will be a matching process of health facilities by proportion of groups of non-medical professionals (nurses and obstetricians) and by availability of basic equipment and maternal and newborn care supplies (the information for which will be available to the health regional directorates), to ensure that health facilities are comparable. Once paired, they will be randomly allocated through a blocked randomization, to ensure a balanced distribution of facilities in each group.

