### Statistical analysis

An intention to treat analysis will be performed, including all clusters as they were initially assigned, including premature withdrawals. Additionally, a per-protocol analysis will be carried out, where only clusters that have completed the study protocol will be considered. The primary outcome will be compared in each arm using Chi-square test if the variable of distribution is normal, or alternatively through the Fisher’s exact test. Secondary outcomes will be compared using the Student’s t-test or the Kruskal-Wallis test. For supplementary oxygen use, the Chi-square test or Fisher’s exact test will be used.

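### Two oxygen outcomes plausibly depend on facility altitude, which is neither matched nor adjusted for, so a chance altitude imbalance across six facilities per arm could look like a training effect

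*Protocol article*

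**What the plan says.** - **Outcomes.** The Secondary objectives list, as items 4 and 5, "Use of supplemental oxygen after 10 minutes of life; 5) Inspiratory oxygen fraction needed at 30 minutes after birth".
- **Terrain.** Under Settings, the two regions are described so: "These regions cover areas of Andean highlands, but their territory is mainly on the Amazon rainforest". No altitude is given for any facility.
- **Eligibility.** The Inclusion and exclusion criteria limit annual births and distance, excluding "facilities located at more than 210 kilometers from the department capital". They set no altitude limit.
- **Matching.** The Randomization section describes a "matching process of health facilities by proportion of groups of non-medical professionals (nurses and obstetricians) and by availability of basic equipment" and related supplies, then random allocation of the paired facilities. Altitude is not named.
- **Analysis.** The Statistical analysis section says "For supplementary oxygen use, the Chi-square test or" Fisher's exact test applies. The oxygen fraction falls under the general rule for secondary outcomes, Student's t-test "or the Kruskal-Wallis test". No covariate, stratum or pair term is named.
- **Unit.** The Study design section makes the facility the unit of both study and analysis. The Sample size section sets 12 facilities, six per arm, averaging 334 deliveries each.

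**The concern.** At a fixed oxygen fraction, inspired oxygen pressure falls as barometric pressure falls. An infant at high altitude may therefore need supplemental oxygen, or a higher fraction, when the same infant in the lowlands would not. Item 5 is itself an oxygen fraction, so altitude bears directly on the quantity measured.

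Six facilities per arm balance an unmatched facility trait poorly. If the arms drew different numbers of highland facilities, both oxygen outcomes would shift together, and the named tests contain nothing to separate that shift from an effect of training. The protocol accepts the general argument, since it matches facilities so that they are comparable. It leaves out a fixed trait that its own description of the setting brings to mind.

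**Working it through.** The protocol gives no figure for the oxygen outcomes, so there is none to reproduce. Its sample size concerns the heart-rate outcome and does not bear on this point.

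**Inputs from the protocol:** 12 facilities, 6 per arm, 334 births each (6 × 334 = 2,004 per arm).

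**Assumptions, because the protocol gives no values:** 4 or 6 of the 12 facilities are highland; the pairing is unrelated to altitude; highland is about 3,000 m and lowland about 500 m; oxygen use is 5% in the lowlands and 5% to 20% in the highlands; facilities are of equal size.

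**1. Chance of imbalance.** Pairing unrelated to altitude makes every 6-6 split equally likely.
- 6 highland: P(difference of at least 2) = 1 − C(6,3)²/C(12,6) = 1 − 400/924 = 56.7%. A difference of at least 4 has 8.0%.
- 4 highland: 1 − C(4,2)·C(8,4)/C(12,6) = 1 − 420/924 = 54.5%. A difference of at least 4 has 6.1%.
- 3 highland: a 2-1 split is the best possible, and 3-0 has 18.2%.
- If every pair were alike in altitude, the chance would be 0%.

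**2. Effect of a split.** A difference of two highland facilities moves the arm difference by (4 − 2)/6 = one third of the highland-lowland gap.

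**3. Oxygen fraction at 30 minutes.** Standard atmosphere: PB = 760(1 − 2.25577×10⁻⁵ h)^5.25588. Inspired oxygen pressure in room air = 0.2095(PB − 47). The fraction equivalent to sea-level room air = 0.2095(760 − 47)/(PB − 47).

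| Altitude (m) | Room-air inspired O₂ pressure (mmHg) | Equivalent fraction |
|---|---|---|
| 500 | 140 | 0.22 |
| 2,000 | 115 | 0.27 |
| 3,000 | 100 | 0.31 |
| 3,800 | 90 | 0.35 |

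For 3,000 against 500 m the gap is 0.31 − 0.22 = 0.09, and one third of it is 0.03. That supposes every infant's fraction is titrated to this equivalent. Infants breathing room air have the same fraction at any altitude. If the same share s is on oxygen in both zones, the shift is about 0.03 × s: 0.03 at s = 100%, 0.015 at 50%, and 0.003 at 10%. The last uses, for illustration only, the share of newborns that the Introduction says may need support at birth.

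**4. Oxygen use after 10 minutes, 4-2 split, no training effect.**
- 5% v 10%: (4×10 + 2×5)/6 = 8.3% against (2×10 + 4×5)/6 = 6.7%, a difference of 1.7 points.
- 5% v 20%: 15% against 10%, a difference of 5 points.

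**5. False-positive rate under no training effect** (simulation; altitude is the only source of variation between facilities).

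| Oxygen use, lowland v highland | Birth-level chi-square, altitude unmatched |
|---|---|
| 5% v 5% | 5% |
| 5% v 7% | 12-13% |
| 5% v 10% | 35-36% |
| 5% v 15% | 56% |
| 5% v 20% | 57-59% |

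Pairing on altitude brings the chi-square to 4.5-5.3% throughout. A facility-level t-test, with altitude still unmatched, gives about 4-8%.

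**The case against.** The case against has several parts.

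- **The text describes regions, not facilities.** A reader might infer that the 12 facilities are known to run from highland to rainforest. The Settings section does not say so. It describes two whole regions with 418 + 848 = 1,266 registered facilities, and the birth-volume, distance and security exclusions may narrow the spread. This stands; the point is conditional on the selected facilities differing in altitude.
- **Randomization makes this chance, not bias.** This also stands. With few clusters, many unmatched traits could be named, and choosing among them for six pairs is a judgement. Altitude earns a place for these two outcomes because its physical link to them is direct and it is known for every site.
- **The pairing may already track altitude.** Staff mix and equipment could be associated with it, so 55-57% is not a firm probability.
- **The inflated error rates belong to another problem.** A reader might take the 12-59% as the cost of ignoring altitude. Most of it comes from testing births as independent, and a facility-level test, which the Study design section already implies, roughly restores the 5% level. What a facility-level test alone does not do is remove a realised imbalance from the estimate or recover precision.
- **Adjustment is often left to an analysis plan.** True, and the absence of a covariate is not in itself the point. The matching factors, however, are fixed here, and the tests named here are unadjusted.
- **Facilities without oxygen.** A reader might also infer that their infants would be scored as not needing it. The article states no such scoring rule, the observation sheet is not shown, and facilities are matched on equipment. That inference is not supported.

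**Conclusion.** The point holds in a limited form. If the 12 facilities differ in altitude and the pairing is unrelated to it, a difference of two or more highland facilities between arms is more likely than not (about 55-57% with 4 or 6 of 12 highland). It could then appear as a training effect on the two oxygen outcomes.

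How large that would be cannot be known from the protocol. The dependence on altitude is physiological reasoning and not a statement in the document. The 0.03 in mean oxygen fraction is an upper figure for a 4-2 split at 3,000 against 500 m and shrinks with the share of infants on oxygen. The 1.7 to 5 points in oxygen use rest on assumed rates. If the chosen facilities lie at similar altitudes, the concern largely disappears, and the investigators can settle that at once.

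Nothing here supports a claim of systematic bias or any claim about the primary outcome. It is a cheap improvement to two of nine secondary outcomes in a trial that calls itself pilot-scale.

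**What to change.** 1. Record the altitude of each of the 12 facilities and report it by arm.
2. In the Statistical analysis section, state that secondary outcomes 4 and 5 will be compared on facility-level summaries, in line with the declared unit of analysis, with altitude as a covariate or as a highland/lowland stratum. Fix the form of the altitude term before the outcome data are seen.
3. Add altitude to the pairing only if allocation has not been done. The Abstract says the study is enrolling, the Secondary objectives section calls it ongoing, and Table 1 places allocation before the eligibility screen, so it may be too late. Steps 1 and 2 remain possible either way.

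**Cost:** one fixed facility-level variable, a sentence or two of text, and one degree of freedom. In an unpaired facility-level comparison the residual degrees of freedom go from 12 − 2 = 10 to 12 − 3 = 9. If altitude proves unrelated to the outcomes, that small loss of precision is the price. If pairing is still open, altitude is a third constraint on forming six pairs and may loosen the match on staff mix or equipment.

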### Effectiveness assessment

After randomization of each facility, standard training or MP-ICT training will be conducted. Evaluations will include a baseline assessment of available equipment and supplies for neonatal resuscitation, immediately after enrolment and before training. To determine the duration of the effects of the intervention, the proposed outcome indicators will be evaluated six months after the training. The primary and secondary outcomes will be assessed intrapartum (within 5 minutes after birth) and postpartum (at 24 hours and 7 days, to know the outcome of the infant). The assessments will be based on an observation sheet (see
Supplementary File 3), in which trained research assistants (registered nurses or equivalent local personnel) will record the activities conducted during the delivery and the birth, and the results of the neonatal resuscitation. The observation of performance in neonatal resuscitation will also be recorded randomly through videos, to verify the validity of the data collected by the research assistant. The videos will be reviewed by the field monitor and by one of the investigators. In order to comply with confidentiality requirements, the videos will be deleted after verification of information.

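### The referral outcome is a raw count with no birth denominator, so it partly tracks facility volume and cannot by itself be read as efficacy

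*Protocol article*

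**What the plan says.** The protocol article's Secondary objectives section lists nine outcomes for comparing the efficacy of the two training arms. Item 6 is "Mortality rate during the first 7 days of life" and item 7 is "Number of referrals to health facilities with greater resolution capacity during the first 7 days of life". The two share a time window, but the first is a rate and the second a number. Items 4 and 5 are "Use of supplemental oxygen after 10 minutes of life" and "Inspiratory oxygen fraction needed at 30 minutes after birth".

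The Statistical analysis section fixes the tests: "Secondary outcomes will be compared using the Student’s t-test or the Kruskal-Wallis test", with one exception, "For supplementary oxygen use, the Chi-square test or Fisher’s exact test will be used". Study design names twelve health facilities as the units of study and analysis, and Sample size puts six in each arm.

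Inclusion and exclusion criteria leaves out facilities with fewer than 290 births a year and sets no upper limit. Randomization describes a "matching process of health facilities by proportion of groups of non-medical professionals (nurses and obstetricians) and by availability of basic equipment" and supplies. Birth volume is not mentioned. Effectiveness assessment follows infants "postpartum (at 24 hours and 7 days, to know the outcome of the infant").

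The article does not give a denominator for referrals, say whether more or fewer referrals is favourable, or say how an infant who dies before a time point is handled.

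**The concern.** Two features make the referral count hard to interpret.

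The first is volume. A facility with twice the births is expected to have about twice the referrals. When facility counts are compared by a t-test or Kruskal-Wallis test, differences in size enter the comparison as variance. If the larger facilities fall by chance in one arm, they also appear as a difference between arms.

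The second is death. Resuscitation training aims to keep alive infants who would otherwise die at or soon after birth. Such an infant contributes no referral if it dies before transfer and one referral if it survives and is transferred. The count can therefore rise because the training works, or fall because more infants die early.

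A related problem affects the two oxygen outcomes. An infant dead by 10 minutes is either counted as not using oxygen or left out. An infant dead by 30 minutes has no oxygen fraction, so that comparison is among survivors only.

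At stake is the reading of one secondary outcome, and to a lesser and unquantified degree two more. The primary outcome is not affected.

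**Working it through.** The article gives no expected figure for referrals, so there is no stated number to reproduce. The checks below show how large the two effects could be.

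**Spread of facility volume**

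- Settings: almost 15,000 deliveries at 80 facilities in 2016, so 15,000 / 80 ≈ 188 a year on average.
- Inclusion and exclusion criteria: floor of 290 a year, or 145 in 6 months.
- Sample size: mean of 334 deliveries per facility in about 6 months, or 668 a year, which is 668 / 290 ≈ 2.3 times the floor. Per arm, 6 × 334 = 2,004.

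The planned mean is well above the floor and there is no ceiling, so eligible facilities can differ widely in size. Their actual spread is not given. I assume a between-facility coefficient of variation (CV) of 0.3 to 0.5.

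**Chance imbalance between arms.** I simulated random splits of twelve facilities, six against six, with mean 334, floor 145 and a log-normal excess above the floor, ignoring the matching. One arm has at least 20% more births in about 28% of splits at CV 0.3 and 49% at CV 0.5. With no training effect, the raw referral totals would then be expected to differ by 20% or more. Matching on staffing and equipment may reduce this if those factors follow volume.

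**Added noise in the facility comparison.** Let *r* be the referral rate, *m* = 334 the mean births, and referrals given births be Poisson. Then the variance of a facility's count is *rm* + (*rm* × CV)², and its ratio to the equal-volume case is 1 + *rm* × CV².

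| Assumed *r* | *rm* | Ratio, CV 0.3 | Ratio, CV 0.5 |
|---|---|---|---|
| 2% | 6.7 | 1.6 | 2.7 |
| 3% | 10.0 | 1.9 | 3.5 |
| 10% | 33.4 | 4.0 | 9.4 |

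Using a proportion removes the volume term, apart from a modest loss because small facilities give less precise proportions. Real differences in referral rate between facilities would add to both versions and make the ratios smaller.

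**Deaths before transfer**

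- Background: neonatal mortality of 15 (Ayacucho) and 20 (Cusco) per 1,000 live births. Per arm this is 2,004 × 0.015 ≈ 30 to 2,004 × 0.020 ≈ 40 deaths, an upper bound for the first 7 days.
- Assumptions: 25% to 100% of these infants die before any referral, training averts 25% to 50% of those deaths, and 50% to 100% of infants saved are referred.
- Extra referrals = deaths × share unreferred × share averted × share then referred.
- Smallest: 30.06 × 0.25 × 0.25 × 0.5 ≈ 0.9. Largest: 40.08 × 1 × 0.5 × 1 ≈ 20.

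That is about 0.05 to 1.0 percentage points of 2,004 births. On an assumed 2% baseline (about 40 referrals), the ratio of better to worse arm is about 1.02 to 1.5. On 10% (about 200), it is about 1.00 to 1.10.

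**What a composite does.** Take 60 referrals and 30 unreferred deaths in the control arm, and suppose training turns 10 of those deaths into referred survivors. Referrals go from 60 to 70 and deaths from 30 to 20. Death or referral is 60 + 30 = 90 in control and 70 + 20 = 90 in the better arm. The reversal disappears, but so does the one-third fall in deaths.

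**The case against.** A reader might infer that the plan scores a dead infant as a good result, so that a programme that saves lives would be judged worse on referral and oxygen. The document does not support that reading. Nothing in it assigns a score to death or names a favourable direction for referrals, and more referrals could equally reflect appropriate care. Rules for infants who die before a time point may stand in an analysis plan that is not shown. Seven-day mortality is compared over the same window, so fewer deaths with more referrals would be visible. Oxygen fraction at 30 minutes has no value in a dead infant, so the issue there is selection of survivors, not a favourable score. Only deaths before 10 or 30 minutes can touch the oxygen outcomes, and the article does not say how many these are.

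All of that stands. It is also true that unequal volume after randomisation is chance imbalance, and that in the worked example the difference of 10 referrals is smaller than its Poisson standard error, √(60 + 70) ≈ 11, even before allowing for clustering.

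These arguments do not answer the denominator point. The outcome is worded as a number next to a mortality rate, volume is uncontrolled, and the facility tests are fixed. Nor does reporting mortality alongside make the count an efficacy measure on its own. With some 30 to 40 deaths per arm at most, the mortality comparison may be too imprecise to explain a referral difference.

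**Conclusion.** The point holds in a limited form. As worded, the referral outcome mixes the referral rate with birth volume. With six facilities per arm, a 20% volume gap is plausible by chance and carries straight into the count. This is a loss of precision and a risk of chance imbalance, not a systematic bias. The 28% to 49% figure rests on the assumed CV of 0.3 to 0.5 and ignores the matching.

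The count also cannot be read as efficacy by itself, because preventing an early death can add a referral. The range of about 1 to 20 extra referrals per 2,004 births rests entirely on assumed timing of deaths, shares averted and shares referred, and the true size may be negligible. For the oxygen outcomes the same concern exists in principle, but no size can be given. The case for replacing the listed outcomes with composites is not made.

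**What to change.** 1. Define item 7 as the proportion of live births referred within 7 days, calculated per facility. Numerator and denominator should cover the same infants, so if only consented births are followed, those births form the denominator.
2. State that this proportion is interpreted together with 7-day mortality and not as an efficacy measure alone.
3. Keep the listed referral and oxygen outcomes. Add as supportive analyses: death or referral within 7 days and, where time of death is recorded, death by 10 minutes or supplemental oxygen after 10 minutes, and oxygen fraction at 30 minutes with earlier deaths ranked worst. Show each component separately.

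Items 1 and 2 need a clause each and the birth counts the trial already relies on. The study is registered and ongoing, so the change should be a dated amendment made before outcomes are compared by arm. Item 3 depends on data that cannot be confirmed here: Effectiveness assessment names observation within 5 minutes of birth, at 24 hours and at 7 days, and the observation sheet is not shown. The composites mix events of different severity and can conceal a mortality benefit, so they should not replace the separate outcomes.
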